## Methods: participants, interventions, and outcomes

### Study setting {9}

Participants across urban and rural Australia self-register for the study via text messaging (SMS) interactions facilitated by the registration component of a bespoke MOTIVATE-C management system, which was developed by the Adaptive Health Intelligence IT team based at the University of Sydney. The study has no designated enrolment nor treatment sites, although the study is promoted nationally through posters and flyers in electronic and print media (see ‘Recruitment {15}’ below).

### Eligibility criteria {10}

To self-register, a person must be an Australian adult (aged 18 years or older) residing in Australia, who is registered for Medicare (Australia’s universal health insurance scheme), and who self-reports as having active HCV infection. A person is ineligible if they:Are already receiving DAA therapy for HCV infection or have received DAA therapy in the previous 6 months,Have previously enrolled in the project,Are unable/unwilling to provide informed consent or to complete follow-up, orAre unable to commence DAA treatment within 12 weeks of registration due to a contra-indication (e.g., pregnancy, or breastfeeding)

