### Trial design {8}

MOTIVATE-C is a pragmatic, factorial, dose–response study that includes sequential analyses and Bayesian adaptive design elements including stopping rules and response-adaptive randomisation. The design has a fixed ‘dose’ (incentive) range for participant incentives, from AUD 0 to AUD 1000 in AUD 50 increments with the AUD 0 dose used as the reference/control dose. For prescribers, the amount of the co-incentive is either AUD 0 or AUD 100.

At the time of registration for the study, participants are randomised to one of the participant incentive amounts. The randomisation weights are balanced across the available incentive amounts until the first interim analysis. While the zero dose retains a fixed allocation weight over the duration of the study, the remaining allocation weights are updated proportional to the updated probabilities that each arm (incentive amount) exceeds a minimal effective dose criterion and that the incentive amounts have a greater probability of response than lower value incentives. The minimum effective dose (MED) criterion is achieved if there is a 0.95 probability that a particular incentive amount results in a ten-percentage point increment (in absolute terms) above the response on the control arm (AUD 0). Futile doses (incentive amounts) are those that have a probability of < 0.2 of being minimally effective and will exit the randomisation which ceases further enrolment to these incentive amounts. If the probability of the MED criterion met is < 0.2 for all incentive amounts, then enrolment will be suspended to consider redesign, necessitating protocol and analysis plan updates.

The design involves regular analyses, which start once all participants enrolled in the first 6 months have reached 12 weeks post-registration, and then every 4 months or after the commitment of AUD100,000, whichever occurs sooner. These analyses will estimate the dose–response curve by fitting a four-parameter EMAX model and calculating the posterior probability of response for all arms. The study will continue until the total study funds available for incentives for participants, co-incentives for nominated primary care prescribers, and compensatory payments (described below) have been expended. A final analysis will be undertaken at the end of the study to address secondary objectives and undertake the economic analyses.

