#### Registration

The SMS-based registration interface (underpinned by the Twilio platform—https://www.twilio.com), once initiated by the participant, prompts the user to respond to a series of self-assessed eligibility questions. Appropriate responses to all eligibility questions progress the potential participant through to successful registration, at which point they will be considered ‘registrants’ and will be informed of the randomly generated incentive amount they will be eligible for in return for providing evidence (within 12 weeks) of initiating DAA therapy. If the registrant confirms through the SMS registration interface that they wish to proceed with the project and are willing to be contacted by a treatment navigator, they are sent a link to the PIS on the project website and informed to expect contact from a treatment navigator within 72 h.

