### Implementation {16c}

The randomisation and allocation processes are coordinated by the MOTIVATE-C management system, which is a microservices application developed by the Health and Clinical Analytics team at the University of Sydney. The system is hosted by University of Sydney with secure access, full audit trial and redundancy. Randomisation functionality is contained within a dedicated service which exposes a RESTful API that can be called by other services within the MOTIVATE-C management system. The mass weighted urn design of the randomisation service produces a random sequence that targets an allocation ratio based on configurable weights. The approach facilitates the implementation of response-adaptive randomisation without major divergence from the specified allocation ratio, which is a problem commonly experienced under response-adaptive randomisation when using simple random sampling.

Registrants initiate their own randomised allocation via the SMS interaction under the previously described response-adaptive allocation scheme. The registrant’s mobile phone number is used to confirm that they are a unique person for the project and not previously registered. If confirmed to be a new registrant, a computer-generated randomised incentive is assigned to the registrant, and they are notified of this by text message. The randomised incentive value is associated with the registrant’s phone number used for the registration. Therefore, if a registrant does not proceed to enrolment after being randomised and then tries to re-register using the phone number used previously for registration, the registrant will not be re-randomised but will be re-notified of their previously assigned incentive.

Prescriber co-incentive allocations are initiated by the navigator via the navigator portal, another component of the MOTIVATE-C management system, only if the participant nominates a preferred prescriber. Again, the implementation of the randomisation sequence is encapsulated within the randomisation microservice, but for prescriber co-incentives, the sequence is simply taken sequentially from pre-generated permuted block randomised sequences with 1:1 allocation to co-incentive or no co-incentive.

In both scenarios, the assigned treatment values are pushed to a dedicated REDCap database, which is used to retain all trial data.

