**Enrolled participants only**		
Name	For participant identification and validation of evidence of testing/prescription/SVR	At the initial meeting with the navigator
Date of birth	To permit adequate description of the study population and validation of evidence of testing/prescription/SVR	
Sex		
Mailing address	Only if participant requests for a hardcopy of the PIS and/or physical gift card to be delivered	
Date of enrolment in the study, *i.e. the date that the participant provides verbal consent to the navigator*	To track compliance with project timelines	At the initial or follow-up meeting (if participant require more time) with the navigator
Date and results of the HCV test	Secondary endpoint and to trigger compensation payment and to track compliance with project timelines	At the navigator-participant meeting to demonstrate evidence of HCV test
Name of the nominated treatment prescriber (including name of the practice)	To enable provision of the compensation payment	At the navigator-participant meeting to demonstrate evidence of DAA prescription
Date of treatment initiation	Primary endpoint and to trigger incentive payment and to track compliance with project timelines	
Adverse events (any untoward health-related events including medical attendance or hospitalisation)	For safety monitoring	At the navigator-participant meeting 2–4 weeks following initiation of treatment
Self-reported number of scheduled/recommended doses of DAA not taken grouped into:	Secondary endpoint	28 days following completion of treatment
• < 7 days,		
• 7–13 days,		
• 14–20 days,		
• 21–27 days,		
• 28 + days		
Date and results of the SVR test	Secondary endpoint and to trigger final compensation payment	4–24 weeks following completion of treatment

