### Methods in analysis to handle protocol non-adherence and any statistical methods to handle missing data {20c}

Missingness is inherent in the study design. Registrants who are insufficiently motivated by the proposed incentive (if any) may choose not to be contacted by a navigator, and participants who fail to initiate therapy with DAA may not contact treatment navigators by 12 weeks post-registration. Navigators will make every reasonable effort to confirm the outcome status of enrolled participants. Failure to enrol or failure to ascertain evidence of successful commencement of DAA therapy by participants will be interpreted as a failure of the intervention.

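### A registrant who declines a low offer can register again on another phone number and be re-randomised, which can create or inflate a dose-response

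*Protocol article*

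**What the plan says.** Trial design {8} places randomisation at the first contact: "At the time of registration for the study, participants are randomised to one of the participant incentive amounts". Under the Registration heading, a person who passes the SMS self-screen "will be informed of the randomly generated incentive amount they will be eligible for in return for providing evidence" of starting treatment, and only then says whether to go on. Enrolment comes later, when verbal consent is given to the navigator.

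Three rules govern repeat attempts.

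- Eligibility criteria {10} lists, among the exclusions, "Have previously enrolled in the project". Prior registration or randomisation is not listed.
- Implementation {16c} says the registrant's "mobile phone number is used to confirm that they are a unique person for the project and not previously registered". A number not seen before is given a fresh random amount by SMS.
- The same section says that if someone who did not go on to enrol "tries to re-register using the phone number used previously for registration, the registrant will not be re-randomised"; they are told their original amount again.

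In Table 2 the phone number is the only identifier taken at registration. Name and date of birth are recorded for enrolled participants only, the name "For participant identification and validation of evidence of testing/prescription/SVR".

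For the analysis, section {20c} treats "Failure to enrol or failure to ascertain evidence of successful commencement of DAA therapy" as failure of the intervention.

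**The concern.** Implementation {16c} plainly intends one random amount per person, but the rules deliver one per phone number. The open route is to register, see a low amount, decline, and register on another phone. The person has not enrolled, so the stated exclusion does not apply, and a navigator following it literally has no ground to refuse them.

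The data set then holds two units for one person: a failure at the low amount and, if treatment starts, a success at the new amount. The error is directional, because the motive to try again is strongest at AUD 0 and vanishes at AUD 1000. It lowers the response at AUD 0, which is the reference for every contrast. If re-registration is concentrated among people who would start treatment anyway, it also raises the response at high amounts. A false gradient would carry into the allocation weights in section {16a}, which use the probability of effectiveness and the step in response from one amount to the next.

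**Working it through.** **Inputs from the article.** There are 21 amounts (AUD 0 to 1000 in steps of 50), equally weighted until the first analysis. The baseline response is about 15% (Sample size {14}). A registrant who does not enrol is a failure ({20c}). A dose is effective if the rise over AUD 0 exceeds 10 points with posterior probability above 0.95 ({20a}).

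**Assumed, because the article gives no figure.** The share who re-register on a new number is taken as 10 to 50%, once per person. The true initiation rate is p = 0.15 at every amount, so any gap is false.

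**The plan's own figures.** Type I error below 6% and an expected 580 participants in the null case come from simulations whose priors and budget are not in the article. They cannot be reproduced here and are not disputed.

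**Model A: the share falls linearly from s at AUD 0 to zero at AUD 1000, and the new offer is the one used.** The mean share is s/2, and second registrations spread evenly over the 21 amounts.

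- Re-registration unrelated to willingness to be treated: each arm has 1 + s/2 registrations per first registration. Response at AUD 0 = p(1 − s/2)/(1 + s/2); at AUD 1000 = p. Gap = ps/(1 + s/2).
- Only would-be initiators re-register: each arm has 1 + ps/2 registrations. Response at AUD 0 = p(1 − s/2)/(1 + ps/2); at AUD 1000 = p(1 + s/2)/(1 + ps/2). Gap = ps/(1 + ps/2).

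**Model B: would-be initiators offered less than AUD 500 (10 of the 21 amounts) re-register with probability r and use the better offer.** Second registrations per arm = 10pr/21 = 0.0714r. Response at AUD 0 = p(1 − 20r/21)/(1 + 0.0714r), because a second draw of AUD 0 (chance 1/21) leaves the success there. Response at AUD 500 to 1000 = (p + 0.0714r)/(1 + 0.0714r).

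| Share (s or r) | A, unrelated: AUD 0 vs 1000 | A, initiators only: AUD 0 vs 1000 | B: AUD 0 vs 500–1000 |
|---|---|---|---|
| 10% | 13.6 vs 15.0 (gap 1.4) | 14.1 vs 15.6 (gap 1.5) | 13.5 vs 15.6 (gap 2.1) |
| 30% | 11.1 vs 15.0 (gap 3.9) | 12.5 vs 16.9 (gap 4.4) | 10.5 vs 16.8 (gap 6.3) |
| 50% | 9.0 vs 15.0 (gap 6.0) | 10.8 vs 18.1 (gap 7.2) | 7.6 vs 17.9 (gap 10.3) |

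Worked example for B at r = 0.5: AUD 0 = 0.15 × 0.5238/1.0357 = 0.0759; high amounts = 0.1857/1.0357 = 0.1793; gap = 0.1034.

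Allowing up to three extra registrations at 50% raises the gap to 9.4 points in model A (initiators only) and to about 11 to 13 in model B, depending on how persistence is modelled.

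**How often a null gradient would be detected.** A one-sided 5% linear trend test was simulated with 580 people and 5,000 runs per setting under model A. It rejects in about 5% of trials with no re-registration, 9% at s = 10%, 15% at 20%, 22–23% at 30% and 44–46% at 50%. This test is a stand-in: it is not the trial's EMAX decision rule, and adaptive randomisation was not modelled.

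**The case against.** The strongest reply is that nothing in the article shows anyone doing this. At submission 186 had been randomised and 116 enrolled, so 70 (70/186 = 37.6%) were not enrolled. Some may still have been pending, and none is shown to be a duplicate. A reader might infer that the trial is producing a false dose-response; the documents support only that it can. This objection stands and limits the claim.

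A reader might also infer that the false gap would by itself produce an effective dose. It would not at modest rates. At the 15% baseline, with one re-registration, only the cut-off model at 50% passes 10 points. Even then, an expected gap of about 10 puts the posterior probability of exceeding 10 near one half, not above 0.95.

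A third tempting reading is that name and date of birth are not used to find duplicates. The article is silent on this, and the full protocol may contain a check. They could expose a second enrolment. They could not be matched to an earlier registration that held only a phone number.

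Finally, collecting little data is deliberate, because many people with HCV are wary of giving personal information (section {18a}). That is a good reason not to demand identity at registration. It does not explain why the exclusion stops at enrolment or why the re-randomisation lock stops at the phone number.

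**Conclusion.** The gap is in the stated rules and should be closed. Sections {10}, {16c} and {20c}, read with disclosure of the amount at registration, allow one person to count as a failure at a low amount and a success at another. The bias favours higher incentives and depresses the AUD 0 reference.

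Its size rests on an assumed re-registration rate and an assumed pattern of behaviour. With a flat 15% true rate and 10 to 50% re-registering once, the expected false gap is about 1.4 to 10 points. At 10% it is roughly 1.4 to 2.1 points: too small to meet the effectiveness criterion alone, but added to any true effect and carried into the allocation weights. No claim is made about how often re-registration occurs, or about the trial's actual error rate, since the EMAX model and adaptive allocation were not run.

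**What to change.** Extend the rule in Implementation {16c} from the same phone number to the same person.

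- Ask in the SMS screen, before the amount is disclosed, and again at the navigator's eligibility check, whether the person has registered before under any number.
- Where an earlier registration is disclosed or found, link the records, honour and analyse the first allocated amount, and count the person once.
- Do not make prior registrants ineligible. That would conflict with {16c}, which lets someone return on the same number at the original amount.
- Report the primary result with and without flagged duplicates.

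The cost is one SMS question, one line in the navigator's script and a linkage rule, with no identity data at registration. Some people lose a second, higher offer. The question relies on honest answers from people with a reason not to give them, so undisclosed duplicates will remain and the bias is reduced rather than removed.

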### Who will take informed consent? {26a}

Treatment navigators are project staff who have a dedicated role which involves one-on-one participant engagement to ensure participant understanding and commitment to the study. The treatment navigator contacts the participant to collect data and monitor their progress at key stages over the 12 weeks following registration.

Consent in MOTIVATE-C occurs in two stages. First stage consent (for registration) is implied when potential participants self-register via the initial SMS in which they report their self-assessed eligibility and desire to learn more from a project treatment navigator. Second stage consent occurs when the registrant is contacted by the treatment navigator who verbally explains what the project entails, including what participant data will be collected according to the ethics-approved participant information sheet (PIS). To proceed, the registrant must have their verbal consent documented by the navigator in the MOTIVATE-C study portal.

### Additional consent provisions for collection and use of participant data and biological specimens {26b}

N/A. There are no additional consent provisions for collection and use of participant data. No biological specimens are collected for the study.

## Interventions

### Explanation for the choice of comparators {6b}

Currently, there is little understanding about what constitutes an effective incentive value in this patient population. In consultation with stakeholders including people with lived experience of HCV infection and with injecting drug use, we have set a range from AUD 0 to 1000 in increments of AUD 50. The upper bound for the incentive values was selected based on stakeholder feedback as the value above which one would expect little incremental gain in the propensity to commence DAA treatment. The lower bound of AUD 0 provides a proxy for the status quo, i.e. absence of a financial incentive. The estimated response on each incentive value will be compared to the reference value (AUD 0) to determine whether it constitutes a minimally effective dose. However, it must be noted that all participants, including those assigned AUD 0 incentive, will have access to the navigator support program and will be eligible for a compensatory payment for HCV testing (see below), so any effect of the interventions need to be interpreted within that context.

### Intervention description {11a}

The intervention is a financial incentive for the participants delivered within the context of a patient support program (i.e. with support from treatment navigators); further details on the nature of the support are provided below. Registrants will be randomised to be eligible for an incentive, ranging in value from AUD 0 to 1000 (inclusive) in AUD 50 increments to be paid on evidence that the DAA medication has been dispensed (DAA treatment initiation) within 12 weeks of registration.

The incentive is offered either in conjunction with, or without, an offer of a co-incentive payment to the participant’s nominated primary care DAA prescriber. This prescriber is randomised (1:1) to a co-incentive payment of AUD 100 or no payment (AUD 0). If the participant does not nominate a preferred primary care prescriber, the participant is referred to a default study prescriber. Default prescribers are not randomised to a prescriber co-incentive payment.

Participants incentives’ and prescribers’ co-incentives are either paid into a digital debit card on a mobile device (smartphone) or else into a physical debit/gift card.

### Criteria for discontinuing or modifying allocated interventions {11b}

The study uses adaptive design features, including response-adaptive randomisation and early stopping rules for futility. The initial randomisation weights are equal across the available incentive values and will be adapted over time to remain proportional to the updated probabilities that (1) each arm exceeds a minimal effective dose criterion and that (2) the incentive amounts have a greater probability of response than lower value incentives.

The interim analyses will estimate the dose–response curve of the incentive value versus treatment initiation relationship by fitting a four-parameter EMAX model for calculating the posterior probability of response for all arms. From the third interim analysis onwards, a futility rule is activated to determine whether a minimum threshold response is present. In the case that the minimum threshold is not met, enrolment will likely be suspended, and alternative dose ranges considered. The study will continue until the total funds available for incentives, co-incentives, and compensatory payments have been expended. No other decision criteria have been pre-specified.

### Strategies to improve adherence to interventions {11c}

The participant is informed by the navigator at their first meeting (and in subsequent follow-up meetings) that, to be eligible for the incentive, evidence of DAA treatment initiation must be provided within 12 weeks of registration. Regardless of any financial incentives offered, the management of all participants is supported by a trained treatment navigator.

### Relevant concomitant care permitted or prohibited during the trial {11d}

All participants will receive support through a personal treatment navigator. Given Australia’s commitment to the World Health Organization’s viral hepatitis strategy for the global elimination of hepatitis C [13], it is possible that other strategies relating to HCV treatment will be available concomitant to the study. This may include use of peer and other support workers, and promotion of point-of-care testing for HCV. While we are not aware of use of financial incentives in Australia, it is conceivable that overlap between MOTIVATE-C and similar initiatives may occur during the lifespan of our study. Participants in other studies and those receiving other supports to assist initiating and/or continuing DAA therapy are not explicitly excluded.

